#### 4.3 SARS-CoV-2 Whole Genome Sequencing

KPSC began saving positive molecular SARS-CoV-2 test specimens in March 2021 to conduct whole genome sequencing (WGS). As part of this effort, all positive SARS-CoV-2 molecular test specimens from March 2021 to February 2022 will be sent to an external laboratory for sequencing and variant identification.

## 5 Study Design Overview

We will conduct an observational cohort study to evaluate the VE of Moderna COVID-19 vaccine in preventing COVID-19 diagnosis and severe COVID-19. Vaccine exposure, COVID-19 outcomes, and covariates will be identified from EHR, as described in Section 7 below. All individuals who receive Moderna COVID-19 vaccine from December 2020 to December 2021 and meet eligibility criteria specified in Section 6.1 below will be included in the study (“vaccinated”, hereafter). The unvaccinated comparator cohort will comprise individuals who have not received Moderna COVID-19 vaccine or any other COVID-19 vaccine as of the index date of their matched vaccinated individual (see Section 6.2 for details on index date) and who meet eligibility criteria specified in Section 6.1 below. Unvaccinated individuals who subsequently receive Moderna COVID-19 vaccine may contribute person-time to both unvaccinated and vaccinated cohorts. Individuals will be followed up through EHR for occurrence of COVID-19 outcomes until the end of the study period (December 31, 2023 for final analysis), or censoring events (termination of KPSC membership allowing for a 31-day gap, death, receipt of a COVID-19 vaccine).

Six interim analyses and a final analysis will be conducted. For the first and second interim analyses, unvaccinated individuals will be randomly selected and n:1 matched to vaccinated individuals by age, sex, and race/ethnicity (if sample size allows), and will be assigned an index date based on the vaccination date of their matched vaccinated individual. For subsequent interim analyses and the final analysis, the number of eligible unvaccinated individuals in the KPSC population may be insufficient for individual matching; if so, frequency matching will be employed. In all analyses, efforts will be dedicated to identifying and adjusting for potential confounders. Cox proportional hazards regression will be used to estimate unadjusted and adjusted HRs. VE (%) will be estimated as  $(1 - \text{adjusted HR}) \times 100$ . Propensity score analyses with inverse probability of treatment weighting (IPTW) will be considered for final analyses.

Analyses will also be conducted for secondary objectives to estimate VE of 2 doses of Moderna COVID-19 vaccine in sub-populations of interest, to estimate VE of 2 doses of Moderna COVID-19 vaccine when received concomitantly with other vaccines, to estimate VE of 2 doses of Moderna COVID-19 vaccine in preventing asymptomatic COVID-19 and symptomatic COVID-19, to estimate durability of 2 doses of Moderna COVID-19 vaccine, and to estimate VE of 1 dose of Moderna COVID-19 vaccine.

We will also conduct analyses to assess VE against specific SARS-CoV-2 variants (Secondary Objectives 16-17). The test-negative and cohort study designs and analytic plan for these analyses are detailed in Section 9 below.

## 6 Study Population

### 6.1 Eligibility Criteria

Individuals will be eligible for inclusion in the study if they meet the criteria below. Index dates are detailed in Section 6.2 below.

#### Inclusion criteria

- Aged  $\geq 12$  years at index date
- KPSC member for  $\geq 12$  months prior to index date through 14 days after the index date (allowing a 31-day gap)  
Membership is necessary to follow-up individuals for COVID-19 outcomes in the EHR. In addition, prior membership allows comorbidities and other covariates to be identified and considered in analyses as potential confounders.

#### Exclusion criteria

- Receipt of a COVID-19 vaccine other than Moderna COVID-19 vaccine prior to or on the index date
- Receipt of 2 doses of Moderna COVID-19 vaccine  $< 24$  days apart [13] for 2-dose exposed cohort
- Receipt of any COVID-19 vaccine  $< 14$  days after the index date
- No health care utilization and no vaccination from the 2 years prior to the index date through the index date
- Occurrence of a COVID-19 outcome  $< 14$  days after the index date

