### 6.2 Index Dates

All individuals meeting criteria in Section 6.1 will be included in analyses. Index dates will be assigned at each analysis. For vaccinated individuals, the index date for Primary Objectives 1-2 and Secondary Objectives 1-13 will be the date of receipt of the second dose of Moderna COVID-19 vaccine. For Secondary Objectives 14-15 among individuals who receive only 1 dose of Moderna COVID-19 vaccine, the index date for vaccinated individuals will be the date of receipt of the first dose of Moderna COVID-19 vaccine.

The index date for the comparison group will depend on the analysis. The comparison group will comprise a similar population meeting criteria in Section 6.1 who are unvaccinated at the index date. For the first and second interim analyses (if sample size allows), unvaccinated individuals will be randomly selected and n:1 matched to the vaccinated individuals by age (12-17 years, 18-44 years, 45-64 years, 65-74 years, and  $\geq 75$  years), sex, and race/ethnicity (Non-Hispanic White, Non-Hispanic Black, Hispanic, Non-Hispanic Asian, and Other/Unknown). The matching ratio will depend on the sample size of the unvaccinated population, between 1:1 to 5:1. The index date for the unvaccinated match will be the same as his/her matched vaccinated counterpart.

For the subsequent interim analyses and final analysis, we expect that there will be insufficient unvaccinated individuals for 1:1 matching, as COVID-19 vaccination is expanded to the general

population. If this is the case, unvaccinated individuals will be randomly selected and matched to the vaccinated individuals by the distribution (frequency) of age, sex, and race/ethnicity of vaccinated individuals. Since frequency matching is not conducted on the individual level, an index date will be assigned to unvaccinated individuals based on the distribution of calendar time of vaccinated individuals on the vaccination (index) date in each age, sex, and race/ethnicity stratum. For example, if 5% of vaccinated individuals are vaccinated during the week of February 1, 2021, 5% of unvaccinated individuals will be assigned an index date of February 1, 2021. Hence, the distribution of index dates between the vaccinated group and the unvaccinated group will be matched. For each interim analysis during the accrual period (December 2020 to December 2021), the comparison group will be assessed and assigned with index dates independently based on all available data.

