## 7 Measures

### 7.1 Exposure Definition

The primary exposure for this study (Primary Objectives 1-2, Secondary Objectives 1-13) will be receipt of 2 doses of Moderna COVID-19 vaccine received  $\geq 24$  days apart (allowing a 4-day grace period prior to the recommended interval of 28 days) during the accrual period. The exposure for Secondary Objectives 14-15 will be 1 dose of Moderna COVID-19 vaccine among individuals who received only 1 dose during the accrual period, and the exposure for Secondary Objective 9 will be receipt of 2 doses of Moderna COVID-19 vaccine during the accrual period, with either dose given concomitantly with another vaccine.

- CVX code: 207
- KPSC Immunization ID and description:
  - 124285 COVID-19, mRNA, LNP-S, PF (Moderna)
  - 124287 COVID-19 vaccine, Moderna, external administration
- Manufacturer: Moderna, Inc
- Product name: Moderna COVID-19 Vaccine
- NDC 10/NDC 11 Labeler Product ID (vial): 80777-273-10 or 80777-0273-10

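### The inactivity exclusion in Section 6.1 counts the study doses, so it can remove inactive members only from the unvaccinated group

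*Protocol*

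**What the plan says.** Protocol Section 6.1 lists as an exclusion: "No health care utilization and no vaccination from the 2 years prior to the index date through the index date". Both conditions must be met for a member to be excluded, and the window includes the index date itself.

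Section 6.2 sets the vaccinated index date. For the two-dose analyses it "will be the date of receipt of the second dose of Moderna COVID-19 vaccine". For Secondary Objectives 14-15, "the index date for vaccinated individuals will be the date of receipt of the first dose of Moderna COVID-19 vaccine".

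The same criteria are meant for the comparators: "The comparison group will comprise a similar population meeting criteria in Section 6.1 who are unvaccinated at the index date". Section 5 defines them as people "who have not received Moderna COVID-19 vaccine or any other COVID-19 vaccine as of the index date of their matched vaccinated individual".

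The Section 6.1 wording does not limit vaccination to vaccines other than the study vaccine, and nothing elsewhere in the protocol disregards the study doses or their visits. The preventive-care covariate in Table 3, by contrast, is expressly limited to other vaccinations.

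**The concern.** An exclusion for inactive members is sensible in an electronic-record study, because people who do not use the system are poorly observed. It should act on both groups alike. Here the exposure itself decides whether the criterion can be met. A vaccinated member with no other contact in two years stays in, while an unvaccinated member with the same history is removed.

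At stake is differential outcome capture. If otherwise inactive members are tested and coded less often at KPSC, keeping them only among the vaccinated lowers observed incidence there, lowers the hazard ratio and raises VE. The rule reaches the two primary objectives and Secondary Objectives 1-15. It also reaches the variant cohort, because Section 10.2 builds that cohort from Sections 6.1 and 6.2. The test-negative analyses have their own criteria in Section 10.1 and are not affected.

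**Working it through.** **Logic check**

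1. Two-dose cohort: "The primary exposure for this study (Primary Objectives 1-2, Secondary Objectives 1-13) will be receipt of 2 doses of Moderna COVID-19 vaccine", given at least 24 days apart. Dose 2 falls on day 0, and dose 1 normally falls earlier in the window. The no-vaccination condition is therefore never met.
2. One-dose cohort: dose 1 falls on day 0, with the same result.
3. The exclusion can therefore remove exactly 0 vaccinated members.
4. Comparators have no COVID-19 vaccine by the index date. One with no utilization and no other vaccine in the window is always removed.
5. A recorded dose does not show that a member uses KPSC care. The exposure codes in Section 7.1 include "124287 COVID-19 vaccine, Moderna, external administration", and Section 13 says outside doses reach the record by manual entry and registry updates.

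**Can covariates repair it?** Utilization is not a matching variable (Sections 6.2 and 7.3). The Table 3 utilization counts cover days -365 to -1, against two years in the exclusion. Comparators with no encounters in the covariate year can still be eligible through contact or a vaccine in the year before, so some overlap remains. For members inactive over the full two years there is no eligible unvaccinated counterpart, and a model must extrapolate. In the two-dose cohort dose 1 normally falls inside the covariate year. If vaccine-only visits count as encounters, which the protocol does not say, an otherwise inactive vaccinated member moves from the 0 category to 1-4.

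**Illustrative size.** The protocol states no figure to reproduce and gives no count of inactive members. Let f be the share of vaccinated members who are otherwise inactive, and r their outcome capture relative to active members. Both are assumed: f = 1-10%, r = 0.3-0.5. Take equal true risk and equal true VE in active and inactive members, only active members among the comparators, and no adjustment:

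observed HR = (1 - VE) × (1 - f + f × r)

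- Smallest case, f = 0.01, r = 0.5: factor = 0.99 + 0.005 = 0.995
- Largest case, f = 0.10, r = 0.3: factor = 0.90 + 0.03 = 0.93

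| True VE | Reads, factor 0.995 | Reads, factor 0.93 |
|---|---|---|
| 0% | 0.5% | 7.0% |
| 50% | 50.25% | 53.5% |
| 70% | 70.15% | 72.1% |
| 90% | 90.05% | 90.7% |

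For example, at 70%: 1 - 0.30 × 0.93 = 0.721. With r = 1 the factor is 1 and there is no bias at all.

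**Against the expected precision.** Take 500,000 vaccinated (the lower end in Section 9), 1:1 comparators, 30 diagnoses per 1,000 unvaccinated and VE 70%. Events are 500,000 × 0.030 = 15,000 and 500,000 × 0.030 × 0.30 = 4,500. The standard error of log HR is √(1/4,500 + 1/15,000) = 0.0170. The 99.3% interval (z about 2.70) is roughly 68.6-71.3%. The upper reading of 72.1% lies outside it and the lower reading of 70.15% lies inside.

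**The case against.** The best defence accepts the literal reading and disputes the consequence.

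- **Capture may be nearly complete.** Section 4 says outside care is captured through claims and deaths come from state and national files. Section 13 says patients are asked about outside positive tests, which are then coded. This stands: it pushes r toward 1, most of all for hospitalization and in-hospital death. A reader might infer that the rule always favours the vaccine. The documents do not support that, since the direction needs r below 1 and they give no value for r.
- **The share may be tiny.** Early accrual favoured healthcare workers, long-term care residents and people aged 65 or over (Section 4.1), who are unlikely to be two-year non-users. This also stands: values of 5-10% for f are an unsupported upper assumption.
- **Adjustment will help.** Table 3 has a zero-encounter category, and Section 7.3 admits any covariate with an absolute standardized difference above 0.1. A zero-category split of 10% against 5% gives 0.05/√[(0.09 + 0.0475)/2] = 0.19, enough to trigger adjustment. This stands in part; the two-year gap remains.
- **Silent comparators may be vaccinated elsewhere.** Section 13 names unrecorded outside vaccination as a risk, so dropping unvaccinated members with no record has a purpose. That purpose does not need the asymmetry: a symmetric rule still removes them.

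**Conclusion.** The asymmetry is certain from the text: eligibility on prior activity depends on exposure. Its effect is conditional. VE is biased upward if otherwise inactive members have less complete outcome capture, and by an amount the documents do not allow one to compute. On the assumed 1-10% inactive and 30-50% relative capture, a true VE of 70% reads about 70.2-72.1% before adjustment. The effect is probably small when VE is high and likely smaller still for severe disease. It grows in VE points as true VE falls, which bears on the yearly durability estimates in Secondary Objectives 12-13.

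A reader might also infer that the two cohorts are not comparable. That goes too far. One criterion acts unequally; age, sex, race/ethnicity and index date are still matched, individually or by frequency, and several utilization measures are candidate covariates.

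**What to change.** In Section 6.1, assess the criterion from day -730 to day -1 in both groups. Disregard COVID-19 vaccine doses, including dose 1 in the two-dose cohort, and visits made only to receive them. Apply the same carve-out to the Table 3 utilization counts if such visits would otherwise count as encounters.

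The cost is one line of text and a code filter. Otherwise inactive vaccinated members leave the cohort. Their number is unknown: under the assumed 1-10% and the 500,000 to 1,000,000 vaccinated expected in Section 9, it would lie between 500,000 × 0.01 = 5,000 and 1,000,000 × 0.10 = 100,000. The VE estimate would then apply to members with some recorded activity, as it already does on the unvaccinated side.

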### 6.2 Index Dates

All individuals meeting criteria in Section 6.1 will be included in analyses. Index dates will be assigned at each analysis. For vaccinated individuals, the index date for Primary Objectives 1-2 and Secondary Objectives 1-13 will be the date of receipt of the second dose of Moderna COVID-19 vaccine. For Secondary Objectives 14-15 among individuals who receive only 1 dose of Moderna COVID-19 vaccine, the index date for vaccinated individuals will be the date of receipt of the first dose of Moderna COVID-19 vaccine.

The index date for the comparison group will depend on the analysis. The comparison group will comprise a similar population meeting criteria in Section 6.1 who are unvaccinated at the index date. For the first and second interim analyses (if sample size allows), unvaccinated individuals will be randomly selected and n:1 matched to the vaccinated individuals by age (12-17 years, 18-44 years, 45-64 years, 65-74 years, and  $\geq 75$  years), sex, and race/ethnicity (Non-Hispanic White, Non-Hispanic Black, Hispanic, Non-Hispanic Asian, and Other/Unknown). The matching ratio will depend on the sample size of the unvaccinated population, between 1:1 to 5:1. The index date for the unvaccinated match will be the same as his/her matched vaccinated counterpart.

For the subsequent interim analyses and final analysis, we expect that there will be insufficient unvaccinated individuals for 1:1 matching, as COVID-19 vaccination is expanded to the general

population. If this is the case, unvaccinated individuals will be randomly selected and matched to the vaccinated individuals by the distribution (frequency) of age, sex, and race/ethnicity of vaccinated individuals. Since frequency matching is not conducted on the individual level, an index date will be assigned to unvaccinated individuals based on the distribution of calendar time of vaccinated individuals on the vaccination (index) date in each age, sex, and race/ethnicity stratum. For example, if 5% of vaccinated individuals are vaccinated during the week of February 1, 2021, 5% of unvaccinated individuals will be assigned an index date of February 1, 2021. Hence, the distribution of index dates between the vaccinated group and the unvaccinated group will be matched. For each interim analysis during the accrual period (December 2020 to December 2021), the comparison group will be assessed and assigned with index dates independently based on all available data.

## 7 Measures

### 7.1 Exposure Definition

The primary exposure for this study (Primary Objectives 1-2, Secondary Objectives 1-13) will be receipt of 2 doses of Moderna COVID-19 vaccine received  $\geq 24$  days apart (allowing a 4-day grace period prior to the recommended interval of 28 days) during the accrual period. The exposure for Secondary Objectives 14-15 will be 1 dose of Moderna COVID-19 vaccine among individuals who received only 1 dose during the accrual period, and the exposure for Secondary Objective 9 will be receipt of 2 doses of Moderna COVID-19 vaccine during the accrual period, with either dose given concomitantly with another vaccine.

- CVX code: 207
- KPSC Immunization ID and description:
  - 124285 COVID-19, mRNA, LNP-S, PF (Moderna)
  - 124287 COVID-19 vaccine, Moderna, external administration
- Manufacturer: Moderna, Inc
- Product name: Moderna COVID-19 Vaccine
- NDC 10/NDC 11 Labeler Product ID (vial): 80777-273-10 or 80777-0273-10

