**Secondary Objective 11:** For Secondary Objective 11, we will calculate VE of 2 doses of Moderna COVID-19 vaccine against symptomatic COVID-19. We will calculate the incidence of symptomatic COVID-19 and estimate unadjusted and adjusted HRs and VEs, as described for the primary analysis above.

**Secondary Objective 12:** For Secondary Objective 12, we will estimate the VE against COVID-19 diagnosis by year. We will calculate COVID-19 diagnosis incidence by follow-up year by dividing the number of incident events occurring within that year by the number of person-years of follow-up for individuals at risk in that year. We will use time-varying Cox regression models to estimate unadjusted and adjusted HRs and VEs, for follow-up Year 1, Year 2, and Year 3 after the index date.

**Secondary Objective 13:** For Secondary Objective 13, we will estimate the VE against severe COVID-19 by year. We will calculate severe COVID-19 incidence, unadjusted and adjusted HRs and VEs, as described for the Secondary Objective 12 analysis above, for follow-up Year 1, Year 2, and Year 3 after the index date.

**Secondary Objective 14:** For Secondary Objective 14, we will estimate the VE against COVID-19 diagnosis among those who only received 1 dose of Moderna COVID-19 vaccine compared to unvaccinated individuals. We will calculate COVID-19 diagnosis incidence, unadjusted and adjusted HRs and VEs, as described for the primary analysis above.

**Secondary Objective 15:** For Secondary Objective 15, we will estimate the VE against severe COVID-19 among those who only received 1 dose of Moderna COVID-19 vaccine compared to unvaccinated individuals. We will calculate severe COVID-19 incidence, unadjusted and adjusted HRs and VEs, as described for the primary analysis above.

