### Exposures

For the 2-dose analysis, the exposure will be defined as receipt of the second dose of Moderna COVID-19 vaccine  $\geq 14$  days prior to the SARS-CoV-2 test date vs. not receiving a dose of any COVID-19 vaccine prior to the SARS-CoV-2 test date.

For the 1-dose analysis, the exposure will be defined as receipt of only 1 dose of Moderna COVID-19 vaccine  $\geq 14$  days prior to the SARS-CoV-2 test date vs. not receiving a dose of any COVID-19 vaccine prior to the SARS-CoV-2 test date.

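### The 1-dose cohort for Objectives 14-15 is selected on whether dose 2 follows, although follow-up starts at dose 1; 1-dose VE is biased downward if infection lowers completion

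*Protocol*

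**What the plan says.** Three sections of the Protocol fix the 1-dose exposed group for Objectives 14-15:

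- Section 7.1 defines the exposure as "1 dose of Moderna COVID-19 vaccine among individuals who received only 1 dose during the accrual period".
- Section 6.2 sets time zero for this group: "the index date for vaccinated individuals will be the date of receipt of the first dose of Moderna COVID-19 vaccine".
- Section 8.4 repeats the restriction for the analysis: VE is estimated "among those who only received 1 dose of Moderna COVID-19 vaccine compared to unvaccinated individuals".

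Section 7.2 counts first events from day 14 after the index date. Section 7.1 gives a recommended dose interval of 28 days, accepts 24 or more, and sets no maximum. Section 11 runs accrual from 12/18/2020 to 12/31/2021.

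The comparator follows a different rule. Under Section 6.2 it consists of people "who are unvaccinated at the index date". Section 5 lets them contribute time until a censoring event, which includes "death, receipt of a COVID-19 vaccine".

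**The concern.** A cohort member's exposure should be known at time zero. Here it is not. Between day 14 and dose 2 a first-dose recipient is already at risk of a counted event, but whether that person belongs to the cohort is still undecided. Someone who stays well and takes dose 2 within accrual is removed with all of their event-free 1-dose time. Someone who is infected in that window and never takes dose 2 within accrual stays in, with the event. If infection makes completion less likely, the outcome helps decide who is exposed, the 1-dose event rate is inflated, and VE is understated.

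Nothing else in the Protocol removes this:

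- The Section 6.1 exclusions for an early outcome or an early further vaccine dose cover only days 0-13.
- Censoring at vaccination cannot help, because people who complete within accrual never enter the 1-dose cohort.
- The Table 3 covariates are measured up to the index date, so adjustment cannot undo selection on later events.
- Section 13 does not list it as a limitation.

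The cut-off also makes retention depend on calendar date. People first vaccinated in about the last four weeks of accrual can hardly complete within it, so nearly all are kept. Earlier recipients are kept only if they do not complete.

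**Working it through.** **Plan's own figures.** The Protocol gives no calculation for Objectives 14-15. Its power figures for the primary objectives do reproduce: Table 5, 0.3 per 1,000, ratio 1 vs 1, VE 70% gives 0.622 against the stated 0.62 (two-proportion z-test, 80,000 vaccinated, two-sided alpha 0.007). Section 9 supplies these inputs:

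- 80,000 two-dose recipients at 80% completion, so 80,000 / 0.8 = 100,000 first-dose recipients, of whom 20,000 stay at one dose.
- Incidence of 30 per 1,000 unvaccinated over 4 months, taken as 122 days: h = 0.030 / 122 = 0.000246 per day.

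**Assumptions not in the Protocol.** True 1-dose VE is 70% and constant; dose 2 falls at day 28; the hazard is constant; there is no confounding. p is the proportion of those infected on days 14-28 who never complete within accrual, and is varied from 0.4 to 0.8. Among everyone else it is 0.2, from the 80% completion.

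**Formula.** Let N be the number of first-dose recipients, T the follow-up days from day 14, and h1 = 0.3h the true 1-dose hazard.

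- Retained cases on days 14-28: N × 14 × h1 × p
- Retained later cases: N × 0.2 × (T − 14) × h1
- Retained person-time: N × 0.2 × T

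The ratio of observed to true rate is r = [14p + 0.2(T − 14)] / (0.2T), and observed VE = 1 − 0.3r. The hazard cancels out.

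| T (days) | p | r | VE read |
|---|---|---|---|
| 122 | 0.4 | 27.2 / 24.4 = 1.115 | 66.6% |
| 122 | 0.8 | 32.8 / 24.4 = 1.344 | 59.7% |
| 365 | 0.4 | 75.8 / 73 = 1.038 | 68.8% |
| 365 | 0.8 | 81.4 / 73 = 1.115 | 66.5% |
| 730 | 0.4 | 148.8 / 146 = 1.019 | 69.4% |
| 730 | 0.8 | 154.4 / 146 = 1.058 | 68.3% |
| any | 0.2 | 1 | 70% (no bias) |

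**Check by simulation.** This used 4 million first-dose recipients, T = 120 and a true VE of 50%. With 60% completion among the infected, VE read 43.8% (formula 44.2%). With 0% completion it read 26.2% (formula 26.7%). With 90% completion, above the 80% of the others, the sign reversed and VE read 53.7%.

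**After the change.** When all first-dose recipients entered at dose 1 and were censored at dose 2, the same simulations, run over 120, 365 and 730 days, returned 49.7-50.7% for a true 50% and 79.8-80.6% for a true 80%.

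**The case against.** The strongest reply concerns size and direction, and much of it stands.

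- **Timing.** Section 8.4 runs Objectives 14-15 at the 4th interim and final analyses; they are not among the select analyses at the 1st and 2nd interims. Follow-up is then longer than 4 months, and the bias falls to about 1-4 points at 365-730 days. This dilution should not be assumed in full, because censoring comparators at vaccination moves the information in a Cox model towards early follow-up.
- **Mechanism.** Infected people who merely delay dose 2 but take it within accrual are dropped with their event, not kept. Only those who never complete within accrual are retained. Early-2021 recipients had most of a year to complete, which weakens the bias.
- **Direction.** It depends on an assumption. The certain part, death before dose 2 under Objective 15, is small: 100,000 × 0.0003 × 0.3 × 14 / 122 ≈ 1 death per 100,000 first doses, applying the same 70% VE to death.
- **Target.** One could say the plan means to study people who stop at one dose. Section 3.2, however, asks for the effectiveness of 1 dose, and under the proposed change people who never complete still contribute all their follow-up.

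A reader might infer that 1-dose VE will read near zero or negative. The documents do not support that: it would need a separate estimate for the days just before dose 2, which is not planned, or a completion rate well above the plan's 80%. Nor do the two 1-dose analyses contradict each other. Section 10.1 defines "receipt of only 1 dose of Moderna COVID-19 vaccine" relative to the test date, which avoids this selection, but it serves Objective 17 under a different design.

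**Conclusion.** The flaw is in the operative text: 1-dose exposure is assigned from post-baseline dose status in one arm only. The understatement of VE is conditional. It requires that infection before dose 2 lowers completion within accrual, which is certain for deaths and a plausible but undocumented assumption for non-fatal infection. It vanishes if infected people complete as often as others and would reverse if they completed more often.

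Under the stated assumptions the loss is about 3-10 percentage points at 4 months and about 1-4 points at 365-730 days, from a true 70%. It would be larger at a lower true VE. Only secondary Objectives 14-15 are affected; the primary 2-dose analyses and the test-negative analyses are not.

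**What to change.** Delete the word *only* from the 1-dose definitions in Sections 6.2, 7.1 and 8.4. Include every first-dose recipient who meets Section 6.1, with the index date at dose 1. Follow from day 14 and censor at dose 2 or another Section 5 censoring event; that section already lists "receipt of a COVID-19 vaccine". An analysis of people who never completed may be kept as a labelled descriptive subgroup.

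The cost is wording in three sections and some extra programming for a larger exposed cohort and its comparators. More of the 1-dose person-time will fall in the short interval before dose 2, so the estimate will lean towards early protection, and the report should say so. The vaccination dates needed are already in the EHR.
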